| Data/ Statistical AnalysisPrimary analysesSpecific aim 1. To develop and validate algorithms to identify patients with anxiety and depression Algorithm development  A systematic review is currently under way to identify the lists of Read codes previously used to define anxiety and depression of primary care databases in the UK. The systematic review search expressions are provided in appendix 5.  *(A) Raw data tabulations*  We will estimate the number and proportion of patients recorded during the observation period with:   1. Diagnostic Read code for anxiety/depression; 2. Prescription of anxiolytics/antidepressants; 3. Referred to mental health services; 4. Symptoms of anxiety/depression.   Proportions will be estimated by calendar year.  *(B) Simpler algorithm*  We will estimate the additional contribution of prescriptions, referrals and symptoms to identify cases of anxiety/depression in CPRD. Referrals and prescriptions of anxiolytics/antidepressants will be considered as sufficient to identify cases of anxiety/depression if a Read code for symptoms of anxiety/depression, respectively, were recorded during the previous year. The reasons for this are threefold: (1) there is good evidence that GPs switched from anxiety/depression diagnostic codes to symptomatic ones [44, 45], following claims of over diagnosis of these conditions; (2) antidepressants and anxiolytics have also other indications, including anxiety disorders for antidepressants [46], which raise questions of the use of these data their own to identify these outcomes; (3) pharmacological treatment of mild depression has been discouraged since 2004 [47], and thus referrals to psychotherapy may help to capture milder cases.  *(C) Complex algorithm*  A more detailed algorithm will be developed considering that some drugs are prescribed for both depression and anxiety, in addition to manage vasomotor symptoms, which may be more frequent in breast cancer survivors than in women who did not have cancer. An example for depression is given in appendix 6. We will estimate the number of patients with anxiety/depression at each step, to evaluate how much each category adds to what has been previously recorded.  Algorithm validation  A random sample of 1 million patients of both sexes will be selected from the CPRD GOLD primary care database. We will apply each algorithm and produce descriptive statistics stratified by likelihood of having the outcome, including:   - Number and proportion of patients with the anxiety, depression or both, by 3-year calendar period; - Number and proportion of patients with the anxiety, depression or both, by 3-year calendar period, age and sex; - Number and proportion of patients with the anxiety and depression by 3-year calendar period and country in the UK.   For each outcome, we will compare the estimates obtained with others obtained from the literature, prioritising national surveys of population-based data such as the following:   - Adult Psychiatric Morbidity Survey 2007 [48] and 2014 [49]; - Measuring National Well-being programme, made available by the Office for National Statistics (includes prevalence of those in the UK with some evidence indicating depression or anxiety, since 2013, by country in the UK and English regions, and by 10-year age groups up to 75 years) [50].   The final algorithm will be chosen by considering information in the numeric value closer to the estimates obtained from the literature. Sensitivity analysis Proportion estimates considering the presence of symptomatic codes within the previous year will be re-calculated to consider shorter periods of time (i.e. 3 and 6 months). Specific aim 2. Risk of mental health outcomes in women who had breast cancer compared to women who did not have cancer**Primary outcomes analysis – depression and anxiety**Main analysis Descriptive statistics including number of events observed and person-years at risk will be computed, overall and stratified by the covariates listed in section M (see above). Medical procedures for the diagnosis of breast cancer are likely to cause anxiety. To deal with this we planned to exclude patients who had a record of anxiety diagnosed within 1 year before the breast cancer; this could result in patients with higher levels of trait anxiety being excluded from the analysis. We will calculate the number and proportion of patients who were excluded because they had the outcome in the year prior to the breast cancer, stratified by month. We will also describe how many of those who were excluded from analysis had an outcome after the breast cancer diagnosis by age-group. The quintiles of the distribution of the number of consultations (defined using the ‘consid’ variable) will be described, as this can indicate the patterns of seeking care between women with a history of cancer, compared to those who did not.  The association between breast cancer history and anxiety and breast cancer history and depression, will be quantified using Cox regression models with time since index as the underlying time scale, and stratifying on matched set to account for matching by age and primary care practice. Follow up will begin at the index date (vide section M for definition of the exposure) and will terminate when an outcome is observed. Women will be censored at the earliest date of any of these: cancer recurrence, other cancer diagnosis, death, transference out of the practice; if these events don’t occur, censoring will be observed at the date of last data collection for the practice. Crude measures of the association between breast cancer history and anxiety and depression will be reported stratifying by the covariates described in section M.  Cox multivariate regression analysis will be use to estimate hazard ratios adjusted for calendar period of breast cancer diagnosis, menopausal status, and diabetes mellitus at baseline (see list of confounders in section L, covariates, for the definition of these variables).  Interaction terms between the exposure and the following variables will be added, to explore effect modification by ethnicity (White, South Asian, Black, Others and mixed), place of residence (care home vs. household), co-habitation status (living alone vs. cohabiting), SES (quintiles of IMD), having mental health disorders history (yes vs. no), having history of stroke (yes vs. no) and coronary heart disease (yes vs. no).  Confidence intervals will be calculated using robust estimates of the standard errors, to account for the fact that patients may also contribute with time at risk in the unexposed cohort prior to their cancer diagnosis.  The proportional hazards assumption will be tested in two ways: 1) graphically, by plotting the cumulative rates on a log scale; 2) inferentially, by applying a likelihood ratio test to the estimates obtained for the entire period of observation and for time split into intervals. Sensitivity analyses Sensitivity analyses planned for this study will include a subset of patients only; this is because they use variables from linked data, which is available for a fraction of the patients only, and include variables amenable to have missing data (i.e. BMI, alcohol intake, smoking and patient-level IMD). Regarding the latter, we will quantify the completeness of each variable to decide on their inclusion in the final models. Analyses including variables with missing data will be restricted to patients with complete data for covariates (complete case analysis), if missing data is likely to be missing not a random. The following sensitivity analyses are planned:   1. The main analysis will be repeated further adjusting for age at diagnosis (continuous variable, since matching allowed for 3-year gap), patient quintile level of IMD, alcohol drinking patterns prior to index date, smoking history and body mass index categories prior to index date. 2. We will exclude women diagnosed with the outcome of interest in the year prior to the cancer diagnosis. To account for the fact that treatment for these conditions may often last for more than one year, and that mild anxiety and depression may be treated in psychological services and not result in visits to the GP, we will repeated the main analysis including only patients who had 5 years of complete follow up prior to the index date and did not have the outcome recorded at any point during this period.  Multiple comparisons We acknowledge that this study includes multiple comparisons for each outcome, and several outcomes. Thus, P-values in the range ~0.01-0.05 be considered as some statistical evidence of an effect and interpreted cautiously. Sample size considerations considering a 0.01 probability of type I error (α) are provided in see section I. Specific aim 3. To estimate association between breast cancer history and anxiety/depression by presence of lymphoedema, pain, mild cognitive impairment, fatigue, sexual dysfunction, sleep disorders, and having done endocrine therapy, during the follow up period. We will estimate the cumulative incidence and period prevalence of lymphoedema, pain, mild cognitive impairment, fatigue, sexual dysfunction, and sleep disorders, in breast cancer survivors during the overall follow up period and by 5-year of follow up period.  We will estimate the hazards of developing anxiety and depression (the main outcomes) for three groups of patients: 1) breast cancer survivors who did not develop the common complication (i.e. lymphoedema, pain, mild cognitive impairment, fatigue, sexual dysfunction, sleep disorders) up to time *t*; 2) breast cancer survivors who have had the common complication at time *t*; 3) women who never had cancer. A Cox regression model will be used to estimate the association between time-updated exposure and the main outcomes (anxiety and depression), having as reference the hazard observed for the women who did not have cancer. The exposure variable will be time-updated; this means that women who develop a common complication will contribute with information to group 1 until the date at which they develop the complication of interest; after this point they will contribute with information to group 2. All models will be adjusted for calendar period of breast cancer diagnosis.  Confidence intervals will be calculated using robust estimates of the standard errors. Sensitivity analyses planned in objective 2 will be applied to this objective as well. Secondary outcomes analyses – fatigue, mild cognitive impairment, pain, sleep disturbance, sexual dysfunction, fatal and non-fatal self-harm The steps outlined above will be repeated for the secondary outcomes. Sensitivity analysis will follow the same rationale as described for the primary analysis. |
| Plan for addressing confounding The confounding effect of age and socio-economic status (SES) will be limited at the study design phase, as  women who had breast cancer will be individually matched to women who never had cancer by age and primary  care practice. Variables considered as important confounders will be included in the multivariate Cox regression  models (vide section M, covariates). |
| Plans for addressing missing data There are no plans for using multiple imputation methods in this study. Three variables in the main analysis are likely to have missing data: body mass index, smoking and alcohol intake. The probability of these values being recorded in the patients’ medical records is likely to depend on the actual value (e.g. obese patients may have their weight more often assessed and smoking may be more often recorded in patients who visit the GP for complications of smoking (e.g. chronic obstructive pulmonary disease). This is a direct violation of the missing at random assumption needed for multiple imputation. We will therefore conduct a complete case analysis, which is a valid method when missingness is conditionally independent of the outcome [52]. |
| Patient or user group involvement (if applicable) No patients were involved in the drafting of this protocol. |
| Plans for disseminating and communicating study results, including the presence or absence of any restrictions on the extent and timing of publication The results of this study will be presented at scientific conferences in the area, and submitted for publication in peer-reviewed journals.  **Conflict of interest statement:** [name] reports that CPRD has financial relationships with its clients, including the London School of Hygiene and Tropical Medicine, in relation to providing access to research data and services outside the submitted work. [name] reports personal fees from Roche, Clinigen, Eli Lilly, and Novartis, not related to this work. [name] reports grants from Wellcome Trust, the Royal Society, Medical Research Council, and British Heart Foundation, outside the submitted work. |
| Limitations of the study design, data sources, and analytic methods Validity of the mental health diagnosis in the CPRD GOLD primary care database  The validity and the completeness of the recording of the mental disorders in CPRD have not been evaluated, and this will limit our results. The diagnosis and treatment of depression has also changed over time, as a result of the 2004 NICE guidelines (discouraging the treatment of mild depression with antidepressants) and the Quality and Outcomes Framework scheme in 2006, which recommended validated questionnaires to evaluate its severity [8, 9]. As for completeness, mental disorders such as depression and anxiety are managed at the primary care level, and therefore the potential for recording is high. Nevertheless, some of these conditions, especially in the sub-threshold or milder severities, may not result in GP visits and go therefore undiagnosed [10].  Unmeasured and residual confounding  This study is also limited by the lack of historical data on potential confounders, such as physical activity. Residual confounding will not be possible to rule out for variables such as smoking [53].  Multiple indications of the psychotropic medicines (complex algorithm definition)  In clinical practice, several classes of pharmacological agents are currently used to manage anxiety and depressive disorders, and many of these pharmacological agents are used to treat other physical and mental disorders (appendix 7). An example of this is illustrated by the guidelines. The National Institute for Health and Care Excellence (NICE) issued guidelines for recognition and management of depression in people who have a physical chronic condition such as cancer [54], and for management of generalized anxiety disorder (GAD) and panic disorder [46]. Low- or high-intensity psychological interventions (e.g. low intensity: individual non-facilitated or guided self-help; high intensity: cognitive behavioural therapy) are recommended as the first line for GAD, mild depression and long-term insomnia (>4 weeks) [46]. Pharmacological treatment is recommended for persisting GAD, moderate to severe depression and insomnia that causes severe daytime dysfunction. SSRI are currently recommended for GAD; benzodiazepines are most often restricted to crisis and not recommended for long-term use [46]. This will raise issues on the indication under which the patient has been prescribed the medicine. We will select all pharmacological agents used to treat each of the outcomes, and seek experts’ advice on which drugs are often prescribed. In any case, this offers a potential for misclassification (thought to be non-differential). |

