| Technical Summary (Max. 300 words) The aim of this study is to estimate the relative risk of anxiety and depression (primary outcomes), and fatigue, pain, sleep disorders, neurocognitive and sexual dysfunctions, and fatal and non-fatal self-harm (secondary outcomes), in breast cancer survivors compared to non-cancer controls. This study will be a matched cohort study, utilising data from the CPRD GOLD primary care database. Outcome-specific algorithms will be developed and validated to identify outcomes in the data. Algorithm development will consider Read codes for diagnoses, prescriptions, referrals and symptoms; prevalence and incidence estimates by age-group and sex will be computed for a random sample of patients selected from CPRD GOLD primary care database. Validation will be against external sources of data, namely published data from population-based surveys in the UK. To estimate the associations between breast cancer survivorship and the primary and secondary outcomes, we will identify all women exposed to breast cancer in the CPRD GOLD primary care database, and randomly select an age- and primary-care-practice-matched cohort of women without prior cancer in a ratio of 1:4. Cox regression models will be used to estimate hazard ratios adjusted for important confounders, and to explore the role of effect modifiers; the proportionality of hazards will be tested graphically and inferentially. |
| Outcomes to be Measured  - Anxiety - Depression - Fatigue - Cognitive impairment - Pain - Sexual dysfunction - Sleep disorders - Completed suicide - Self-harm |

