| Feasibility counts Feasibility counts presented below are based on the January 2018 version of the CPRD GOLD primary care database.  We identified 65,136 women who had a diagnosis of breast cancer (Read codes provided in appendix 2) while aged between 18 and 80 years, registered with a primary care practice contributing with data to CPRD, and whose individual records were acceptable for research. Non-interrupted one year of follow up before the cancer diagnosis (index date) was not available for 6,757 women, and 6,044 women were further excluded because they had a lifetime diagnosis of severe mental illness or another cancer before their breast cancer diagnosis (see section J for the inclusion and exclusion criteria).  Hence, 52,335 women with a history of breast cancer were identified as eligible for this study; the table below provides details of the distribution by age and calendar period of diagnosis.  Table 1 Distribution of women with breast cancer history who are eligible for this study, by age and calendar period of diagnosis.   \|  \| **N** \| **%** \| \| --- \| --- \| --- \| \|  \|  \|  \| \| **All study participants** \| **52,335** \| **(100.0)** \| \|  \|  \|  \| \| **Calendar period of diagnosis** \|  \|  \| \| 1989-1994 \| 3,184 \| (6.1) \| \| 1995-1999 \| 4,768 \| (9.1) \| \| 2000-2004 \| 10,934 \| (20.9) \| \| 2005-2009 \| 14,705 \| (28.1) \| \| 2010-2014 \| 13,805 \| (26.4) \| \| ≥2015 \| 4,939 \| (9.4) \| \|  \|  \|  \| \| **Age at diagnosis (years)** \|  \|  \| \| 18-24 \| 24 \| (0.1) \| \| 25-34 \| 771 \| (1.5) \| \| 35-44 \| 4,916 \| (9.4) \| \| 45-54 \| 12,235 \| (25.3) \| \| 55-64 \| 14,910 \| (28.5) \| \| 65-74 \| 12,811 \| (24.5) \| \| 75-80 \| 5,668 \| (10.8) \| \|  \|  \|  \|   A comparison group of women without cancer (4 controls per breast cancer case) will be randomly selected from the same data source, same primary care practice and within a 3-year age range.  Appendix 2 provides the list of Read codes used to identify women with a history of breast cancer in the CPRD GOLD primary care database. The list of Read codes used to identify cancer diagnoses other than the breast one (exclusion criterion) has been published elsewhere [14]. A provisional list of Read codes to identify women with several mental illnesses (exclusion criterion) was defined for the purpose of this calculation; the final list will be refined in due course. |

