| Sample size considerations Table 2 shows the minimum relative risk that could be detected with the 52,335 women identified in the CPRD GOLD primary care database, for different probabilities of type I (α) and type II error (β). These estimates were obtained with the command ‘power’ in Stata v15 [15].  Table 2 Minimum RR that can be detected with the 52,355 women with a history of breast cancer and 209,420 women who did not have cancer, for different probabilities of type I and type II errors, and baseline risk of the outcomes.   \| **Outcome** \| **α** \| **β** \| **% of outcome in unexposed group [ref]** \| **Min. HR possible to be estimated** \| \| **RR/HR estimated in other studies [ref]** \| \| \| --- \| --- \| --- \| --- \| --- \| --- \| --- \| --- \| \|  \|  \|  \|  \|  \| \|  \| \| \| **Primary outcomes** \|  \|  \|  \|  \| \|  \| \| \|  \|  \|  \|  \|  \| \|  \| \| \| **Anxiety, diagnoses** \| **0.05** \| **0.20** \| **5 [7]** \| **1.05** \| \| 1.06 [7]  1.08 [7]  1.22 [11]  1.25 [8] \| \| \| **0.01** \| **0.20** \| **5 [7]** \| **1.06** \| \| \| **0.05** \| **0.10** \| **5 [7]** \| **1.06** \| \| \| 0.01 \| 0.10 \| 5 [7] \| 1.07 \| \| \|  \|  \|  \|  \| \| \| **0.05** \| **0.20** \| **20 [11]** \| **1.02** \| \| \| **0.01** \| **0.20** \| **20 [11]** \| **1.03** \| \| \| **0.05** \| **0.10** \| **20 [11]** \| **1.03** \| \| \| **0.01** \| **0.10** \| **20 [11]** \| **1.03** \| \| \|  \|  \|  \|  \|  \| \|  \| \| \| **Anxiety, prescription of**  **anxiolytics** \| **0.05** \| **0.20** \| **3 [10]** \| **1.07** \| \| 1.08 [7]  2.52 [10] \| \| \| **0.01** \| **0.20** \| **3 [10]** \| **1.08** \| \| \| **0.05** \| **0.10** \| **3 [10]** \| **1.08** \| \| \| 0.01 \| 0.10 \| 3 [10] \| 1.09 \| \| \|  \|  \|  \|  \| \| \| **0.05** \| **0.20** \| **8 [7]** \| **1.04** \| \| \| **0.01** \| **0.20** \| **8 [7]** \| **1.05** \| \| \| **0.05** \| **0.10** \| **8 [7]** \| **1.05** \| \| \| **0.01** \| **0.10** \| **8 [7]** \| **1.06** \| \| \|  \|  \|  \|  \|  \| \|  \| \| \| **Depression, diagnoses** \| 0.05 \| 0.20 \| 3 [11] \| 1.07 \| \| 1.06 [7]  1.39 [9]  1.49 [8]  1.94 [11] \| \| \| 0.01 \| 0.20 \| 3 [11] \| 1.08 \| \| \| 0.05 \| 0.10 \| 3 [11] \| 1.08 \| \| \| 0.01 \| 0.10 \| 3 [11] \| 1.09 \| \| \|  \|  \|  \|  \| \| \| **0.05** \| **0.20** \| **9 [7]** \| **1.04** \| \| \| **0.01** \| **0.20** \| **9 [7]** \| **1.05** \| \| \| **0.05** \| **0.10** \| **9 [7]** \| **1.04** \| \| \| **0.01** \| **0.10** \| **9 [7]** \| **1.05** \| \| \|  \|  \|  \|  \|  \| \|  \| \| \| **Depression, prescription of**  **antidepressants** \| **0.05** \| **0.20** \| **2 [10]** \| **1.08** \| \| 1.16 [7]  1.95 [10] \| \| \| **0.01** \| **0.20** \| **2 [10]** \| **1.10** \| \| \| **0.05** \| **0.10** \| **2 [10]** \| **1.09** \| \| \| **0.01** \| **0.10** \| **2 [10]** \| **1.11** \| \| \|  \|  \|  \|  \| \| \| **0.05** \| **0.20** \| **20 [7]** \| **1.02** \| \| \| **0.01** \| **0.20** \| **20 [7]** \| **1.03** \| \| \| **0.05** \| **0.10** \| **20 [7]** \| **1.03** \| \| \| **0.01** \| **0.10** \| **20 [7]** \| **1.03** \| \| \|  \|  \|  \|  \|  \| \|  \| \| \| **Secondary outcomes *** \|  \|  \|  \|  \| \|  \| \| \|  \|  \|  \|  \|  \| \|  \| \| \| **Sexual dysfunction** \| 0.05 \| 0.20 \| 4.1 [16] \| 1.06 \| \| 1.03 [16]  2.27 [17] \| \| \| 0.01 \| 0.20 \| 4.1 [16] \| 1.07 \| \| \| 0.05 \| 0.10 \| 4.1 [16] \| 1.07 \| \| \| 0.01 \| 0.10 \| 4.1 [16] \| 1.08 \| \| \|  \|  \|  \|  \| \| \| 0.05 \| 0.20 \| 9.1 [17] \| 1.04 \| \| \| 0.01 \| 0.20 \| 9.1 [17] \| 1.05 \| \| \| 0.05 \| 0.10 \| 9.1 [17] \| 1.04 \| \| \| 0.01 \| 0.10 \| 9.1 [17] \| 1.05 \| \| \|  \|  \|  \|  \|  \| \|  \| \| \| **Suicide** \| 0.05 \| 0.20 \| 0.0008** [18] \| 1.47 \| \| 1.37 [18]  1.6 [19] \| \| \| 0.01 \| 0.20 \| 0.0008** [18] \| 1.60 \| \| \| 0.05 \| 0.10 \| 0.0008** [18] \| 1.57 \| \| \| 0.01 \| 0.10 \| 0.0008** [18] \| 1.70 \| \| \|  \|  \|  \|  \|  \| \|  \| \| \| **Fatal and**  **non-fatal self-harm** \| 0.05 \| 0.20 \| 0.005 [18, 20] \| 1.17 \| \| 1.03 [21]  1.37 [18] \| \| \| 0.01 \| 0.20 \| 0.005 [18, 20] \| 1.21 \| \| \| 0.05 \| 0.10 \| 0.005 [18, 20] \| 1.20 \| \| \| 0.01 \| 0.10 \| 0.005 [18, 20] \| 1.24 \| \| \|  \|  \|  \|  \|  \| \|  \| \| \| **Sleep disturbances** \| 0.05 \| 0.20 \| 50 [22] \| 1.01 \| \| 0.8 [22] \| \| \| 0.01 \| 0.20 \| 50 [22] \| 1.02 \| \| \| 0.05 \| 0.10 \| 50 [22] \| 1.02 \| \| \| 0.01 \| 0.10 \| 50 [22] \| 1.02 \| \| \|  \|  \|  \|  \|  \| \|  \| \| \| **Prescription of hypnotics** \| **0.05** \| **0.20** \| **4 [23]** \| **1.06** \| \| 3.75 [23] \| \| \| **0.01** \| **0.20** \| **4 [23]** \| **1.07** \| \| \| **0.05** \| **0.10** \| **4 [23]** \| **1.07** \| \| \| **0.01** \| **0.10** \| **4 [23]** \| **1.08** \| \| \|  \|  \|  \|  \|  \| \|  \| \| \| **Mild cognitive impairment** \| **0.05** \| **0.20** \| **5 [24]** \| **1.05** \| \| 1.58 [25]  1.60 [26]  2.43 [24]  3.67 [27] \| \| \| **0.01** \| **0.20** \| **5 [24]** \| **1.06** \| \| \| **0.05** \| **0.10** \| **5 [24]** \| **1.06** \| \| \| **0.01** \| **0.10** \| **5 [24]** \| **1.07** \| \| \|  \|  \|  \|  \| \| \| **0.05** \| **0.20** \| **19 [26]** \| **1.02** \| \| \| **0.01** \| **0.20** \| **19 [26]** \| **1.03** \| \| \| **0.05** \| **0.10** \| **19 [26]** \| **1.03** \| \| \| **0.01** \| **0.10** \| **19 [26]** \| **1.04** \| \| \|  \|  \|  \|  \| \|  \| \|  \| \|   HR – hazard ratio. RR – risk ratio. Bold is used to denote where the minimum risk ratio that could be detected with the available sample size is lower than the lowest estimate reported in the literature.  * No population-based studies have been identified reporting the relative risk of sexual dysfunctions, pain, fatigue, sleep disorders or cognitive dysfunction in breast cancer survivors compared to the non-cancer female population. Thus, the relative risk reported in the column for the other studies comes from studies involving convenience samples of cancer survivors. Pain and fatigue are often evaluated using psychometric instruments whose mean scores are summarised as means for between-group comparisons; no studies were identified providing data for the prevalence of pain and fatigue in breast cancer survivors and in women who did not have cancer, and thus these two outcomes were not included in the table.  ** Calculated as the proportion of suicides in the exposed group divided by the inverse of the standardised mortality ratio reported in the original study.  The available sample size is expected to be sufficient for detecting clinically significant increases of anxiety and depression (primary outcomes) in breast cancer survivors compared to the women who did not have cancer.  For the secondary outcomes, sample size is likely to be enough to assess differences in sleep disturbance measured by hypnotics’ prescription, and mild cognitive impairment. However, the available sample size will have relatively small power to detect small differences in suicide between women with history of breast cancer and those who did not have cancer, because this is a rare outcome, but we will still have enough power to detect associations of a magnitude seen in some previous studies; data from our analysis can also contribute to future meta-analyses. |

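### The minimum detectable HRs in Table 2 do not follow from the stated 1:4 group sizes; they match the same total split 1:1, and so overstate power

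*Protocol*

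**What the plan says.** The Technical Summary plans to "randomly select an age- and primary-care-practice-matched cohort of women without prior cancer in a ratio of 1:4". Feasibility counts repeats this: "A comparison group of women without cancer (4 controls per breast cancer case) will be randomly selected". Study Design and the section on selecting controls say up to four per case.

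The text of Sample size considerations says: "Table 2 shows the minimum relative risk that could be detected with the 52,335 women identified in the CPRD GOLD primary care database". The caption of Table 2 gives slightly different counts: "Minimum RR that can be detected with the 52,355 women with a history of breast cancer and 209,420 women who did not have cancer". Either way, one woman in five is exposed.

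The table has 16 outcome and baseline blocks, each with four pairs of alpha and beta (0.05/0.20, 0.01/0.20, 0.05/0.10, 0.01/0.10), so 64 minimum HRs. The source given is the Stata v15 power command, without subcommand or options. Bold marks cells whose minimum lies below the lowest published estimate.

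From the table the protocol concludes that the sample is sufficient for clinically significant increases in anxiety and depression. For suicide it first concedes limited power for small differences, then says "we will still have enough power to detect associations of a magnitude seen in some previous studies". The Multiple comparisons paragraph refers back to the alpha 0.01 figures.

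**The concern.** For a fixed total and baseline risk, a 1:4 split carries less information on a hazard ratio than a 1:1 split. The variance of the exposure indicator is 0.2 × 0.8 = 0.16 instead of 0.5 × 0.5 = 0.25. A power calculation that leaves the exposure SD at 0.5 therefore returns minimum HRs that are too small. The printed values look like the output of such a calculation.

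Table 2 is the protocol's only quantitative evidence on power. It decides which outcomes are described as adequately powered, which cells are bold, and what can be said about suicide. The alpha 0.01 rows, to which the multiplicity paragraph points, would be the most affected.

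**Working it through.** **Inputs.** N = 52,355 + 209,420 = 261,775 (caption); 5 × 52,335 = 261,675 gives the same results to the precision used. Baseline risk p, alpha and beta come from Table 2. Sidedness is not stated, so two-sided is assumed. The planned analysis is Cox regression and the results column is a minimum HR.

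**Formula (Cox/Schoenfeld, events taken at the baseline risk).** HR = exp[(z_α/2 + z_β) / (SD × √(N p))], with SD = √(w(1−w)) and w the exposed fraction. SD is 0.5 at 1:1 and 0.4 at 1:4. The sum z_α/2 + z_β is 2.802, 3.417, 3.242 and 3.857 for the four alpha/beta pairs in table order.

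**Reproducing the printed figures.** Suicide, p = 0.0008: N p = 209.4 and √(N p) = 14.47.
- 1:1: exp(2.802 / 7.236) = 1.473; printed 1.47.
- 1:4: exp(2.802 / 5.789) = 1.62.

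| Baseline | Printed | 1:1 | 1:4 |
| --- | --- | --- | --- |
| 5% | 1.05/1.06/1.06/1.07 | 1.050/1.062/1.058/1.070 | 1.063/1.078/1.073/1.088 |
| 3% | 1.07/1.08/1.08/1.09 | 1.065/1.080/1.076/1.091 | 1.082/1.101/1.096/1.115 |
| 9% | 1.04/1.05/1.04/1.05 | 1.037/1.046/1.043/1.052 | 1.047/1.057/1.054/1.065 |
| Self-harm (0.005) | 1.17/1.21/1.20/1.24 | 1.168/1.208/1.196/1.238 | 1.21/1.27/1.25/1.31 |
| Suicide (0.0008) | 1.47/1.60/1.57/1.70 | 1.473/1.604/1.565/1.704 | 1.62/1.80/1.75/1.95 |

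Over all 64 cells, 1:1 matches 60 to two decimals and the other four within 0.01; 1:4 matches 3. Solving the suicide cells for w(1−w), allowing for rounding, gives 0.243 to 0.257: this includes 0.25 and excludes 0.16.

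**Other formulas at 1:4.** A two-sided two-proportion test with 52,335 and 209,340 women matches 17 of 64 cells (suicide 1.53/1.65/1.63/1.76). No two-sided 1:4 variant tried reproduces the table. The closest 1:4 variant, one-sided two proportions, roughly fits suicide but gives 1.18/1.23/1.21/1.26 for self-harm.

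**Size under the Cox formula.** The ratio of log HRs, 1:1 to 1:4, is √(0.16/0.25) = 0.80. Power at the unrounded 1:1 HR under 1:4 is Φ[0.8(z_α/2 + z_β) − z_α/2]:
- alpha 0.05: 61.1% (nominal 80%) and 73.7% (nominal 90%);
- alpha 0.01: 56.3% and 69.5%.

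**Bold cells at 1:4 (Cox).** Seven are not below the lowest published estimate: three for anxiety diagnoses at 5% (1.063, 1.078, 1.073 against 1.06), three for anxiolytics at 3% (1.082, 1.101, 1.096 against 1.08) and one for depression diagnoses at 9% (1.065 against 1.06). Four of them were printed as ties (1.06 twice, 1.08 twice), so they did not meet the bold rule even as printed.

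**Suicide, alpha 0.05, 1:4.** The minimum HR at 80% power is 1.62 with baseline events, 1.58 with events counted under the alternative and 1.53 by two proportions. Power at 1.6 is about 78%, 82% and 88% respectively. Power at the other cited estimate, 1.37, is between 45% and 54%.

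**Units.** The suicide and self-harm baselines stand in a percent column ("of outcome in unexposed group [ref"), but the printed HRs arise only if 0.0008 and 0.005 are proportions. Read as percentages they would mean about 2 events (0.000008 × 261,675 = 2.1) and 13 events (0.00005 × 261,675 = 13.1) in the whole study.

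**The case against.** The strongest reply is that the table drives nothing. The cohort takes every eligible woman in an existing database, so no recruitment target depends on it, and most cited effects for the primary outcomes (up to 2.52) remain detectable. This stands: the conclusion on anxiety and depression is weakened only for the smallest published effects.

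It is also fair that the command options are not shown, that RR and HR are used interchangeably, and that neither formula models the Cox analysis stratified on matched set. The 1:1 split is therefore an inference from the match, and the corrected values are those of one formula. The mismatch between the printed HRs and the captioned group sizes does not depend on that inference.

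Three stronger readings are tempting and are not supported.
- **That every log HR is 20% too small whatever the method.** By two proportions the suicide log RR is about 9% too small (ln 1.47 / ln 1.53 = 0.91). At a 50% baseline the minima are 1.014/1.017/1.016/1.019 against printed 1.01/1.02/1.02/1.02, which is no shortfall.
- **That power at each printed HR is 61% or 74%.** Those figures belong to the unrounded 1:1 HRs at alpha 0.05. At the printed two-decimal HRs and alpha 0.05, Cox power at 1:4 runs from about 30% to 68% in the beta 0.20 rows and 67% to 82% in the beta 0.10 rows.
- **That the suicide sentence is refuted because 1.62 exceeds 1.6.** Two other reasonable calculations fall below 1.6, and the sentence speaks only of some previous studies. It is borderline.

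The unit slip changes no computed HR, and the footnote on suicide already speaks of a proportion. It is a labelling correction.

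**Conclusion.** The point holds. The minimum HRs in Table 2 are inconsistent with the 1:4 group sizes in its own caption and agree almost completely with a 1:1 split of the same total. Under the Cox formula, two-sided and with events at the baseline risk, the detectable log HRs should be 1.25 times those printed, with the power shortfall shown above. Other formulas give a smaller gap for rare outcomes.

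The consequences are limited. Seven bold flags for the primary outcomes are not justified at 1:4, four of which were doubtful as printed. Power for suicide is roughly 80% only at the largest cited estimate (1.6, alpha 0.05) and about half at 1.37. The study remains able to detect the larger published effects for anxiety and depression.

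**What to change.** - Recompute Table 2 with the exposed fraction at 0.2 (covariate SD 0.4). State the subcommand or formula, the sidedness and how events are counted.
- Restate all minimum HRs and redo the bold flags against the table's own rule, settling how ties are treated.
- Qualify the suicide sentence: roughly 80% power at an HR of 1.6 and alpha 0.05, about half at 1.37.
- Label the suicide and self-harm baselines as 0.08% and 0.5%, and align the two counts of exposed women (52,335 in the text, 52,355 in the caption).
- Note beside the table that N does not yet reflect the exclusion of women with the outcome in the year before index. That count cannot be computed until the outcome code lists are defined under aim 1.

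The cost is one command per row, one table and a few sentences. The stated power becomes somewhat less favourable. No design change and no extra patients are needed.
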